#### In addition to the clinical endpoints, the investigators will evaluate surrogate makers for HIV disease progression and risk for tuberculosis. A series of analyses will be performed to describe viral kinetics in the first 3 months after starting therapy and to evaluate predictors of virologic and immunologic response to punctuated therapy. This analysis will also evaluate predictors of viral diversity and drug-resistance during and after the study intervention. A general approach to the analysis of censored biomarker measurements will be used to compare group responses.88 Investigators will also evaluate immune reconstitution during treatment for TB both with and without antiretroviral therapy. In this analyses, we will measure and compare serial responses to both HIV and TB specific antigens in whole blood cytokine assays, ElISpot assays, and activation markers (e.g., CD38, HLADR, CD4 and CD8). Archived samples collected as a routing part of the study will be used for these analyses

####

#### **10.2.2.4** **Additional Analyses**

The primary analysis as described will be performed according to the principles of intention to treat. In the event of withdrawal secondary to ineligibility, non-adherence, refusal, or toxicity, we will perform subgroup analyses of patients as treated, stratified by the degree of adherence. Propensity scores will be generated to capture the likelihood of non-adherence. Using the propensity scores, we will stratify patients according to the scores and examine the effect within and across strata. If the results of this ancillary analysis concur with the intention-to-treat analysis, then the interpretation of the results will be straightforward. If the results of this analysis differ from the intention-to-treat analysis, then the intention-to-treat analysis will be reported as the primary results because it is least likely to be biased.

## 10.3 Interim Analysis and Stopping Rules

### **10.3.1 Interim Analysis**

An interim analysis will be performed a few weeks after the first 20 subjects have been randomized into the study and have entered Step 2. A report of these cases will be submitted to the DSMB and the sponsor. For the remainder of the study, interim analyses will be performed annually. For each interim analysis, a standardized test statistic will be calculated for the main outcome (progression of HIV disease) based on accrued data. If this statistic exceeds the nominal critical value calculated using the error spending function (Table 10), then a statistically significant result will have been achieved at the time of that analysis. The sponsor will be notified and a report submitted for review by the NIAID Data Safety Monitoring Board (DSMB). In each interim analysis, the study team will present information on recruitment and the results of interim analyses to the DSMB which will review the data and recommend a course of action.

**Table 10. Schedule of 5 annual interim analyses to monitor disease progression**

This analysis assumes α=0.05 (two-sided test), O’Brien-Fleming boundaries (DeMets error-spending function), a rate of progression of 50% per year in the reference group and 25% per year in the treated group, and 350 trial participants.

| Year | Time | Information | Lower Bound | Upper Bound | Alpha | Cumulative alpha |
| --- | --- | --- | --- | --- | --- | --- |
| 1 | 0.2 | 0.29 | -4.8769 | 4.8769 | 0.00000 | 0.00000 |
| 2 | 0.4 | 0.50 | -3.3569 | 3.3569 | 0.00079 | 0.00079 |
| 3 | 0.6 | 0.62 | -2.6727 | 2.6724 | 0.00683 | 0.00762 |
| 4 | 0.8 | 0.76 | -2.2759 | 2.2550 | 0.01681 | 0.24420 |
| 5 | 1.0 | 0.83 | -1.9851 | 1.9612 | 0.02558 | 0.05000 |

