**Table 9. CD4+ cell decline before and after TB in Ugandan adults**

| Study Group | N | Rate of change in CD4+ |
| --- | --- | --- |
| Observational Cohort | 230 | One year: -83 cells/μL  Two Years: -162 cells/ μL |
| Incident TB cases | 15 | Before TB: -11.9 cells/month  After TB: -8 cells/month |
| TB Cases after treatment | 95 | Mean decline: -8.7 cells/month |

The rate of decline in CD4+ cell count has been estimated in two different groups of TB patients in Uganda (Table 9). Based on these findings, we estimate a decline of between 7 to 10 cells/month in the reference group. We therefore expect that the CD4+ count will decline at a similar rate in the TB patients receiving anti-TB treatment only and possibly delayed ARV therapy.

Effect size (ES) was used to determine power along a range of sample sizes. ES is defined as: , where λe and λr are the hazard rates for disease progression for the exposed and reference groups, respectively.73 In this trial, the exposed group will receive punctuated therapy and the reference group will receive anti-TB treatment only with possible delayed ARV therapy. The ratio of hazard rates, λe/λr, is the relative hazard and is an estimate of the relative risk for disease progression in the exposed compared with the reference group. In this analysis, we used the Cox-Mantel test to simulate power for samples sizes from 0 to 300 subjects per arm (Figure 5A and 5B) under two scenarios (see figure legend for assumptions). In one scenario, the rate of disease progression in the reference group was 50% at two years (Figure 5A), and in the other, the rate was 50% at 3 years (Figure 5B).

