**Figure 5. Sample Size Calculation**

Power of designed study according to sample size per arm and effect size. Assumptions in calculations: alpha=0.05 (2 tailed), 1600 simulations, 95% confidence intervals for estimated proportions, a 3-year accrual period, and 5% dropout per year, constant hazard throughout period, and Cox Mantel-Haenszel test statistic for the comparison of two survival distributions.74 (A.) 50% disease progression by 2 years in reference group; (B.) 50% disease progression by 3 years in reference group, i.e., slower disease progression than expected. The simulations were implemented using N QueryAdvisor.75

Under the assumption that 50% of patients in the reference group will progress to CD4+ count < 250/µL within 2 years and an effect size of 35%, a power of 80% would be achieved with 125 TB patients per arm, and 90% with 175 patients per arm. Under the assumption that 50% of patients in the reference group will progress to CD4+ count < 250 within 3 years and an effect size of 35%, a power of 80% would be achieved with 175 subject per arm, and 90% with 250 subjects per arm. Based on this analysis, we chose a sample size of 175 TB patients per arm for a total of 350 TB patients. The sample size of 350 TB patients also ensures a large enough sample size to examine secondary outcomes with power of 80% or greater in each comparison.

Figure 5.

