10.3.2 Stopping Rules

The DSMB will determine whether to stop the study after a thorough review of interim data. The DSMB’s decision to stop the study will be guided by the critical values shown in Table 10. If, during an interim analysis, the critical value crosses the O’Brien-Fleming boundary, then the study will be stopped on statistical grounds as a significant difference between arms will have been observed. To evaluate trends in adverse events and deaths between the annual reviews of the DSMB, the study team will provide interim safety reports to the DAIDS Medical Monitor, and possibly a DSMB representative, pending discussion of the overall safety monitoring plan with the DSMB committee. These reports will provide cumulative enrollment figures, cumulative deaths and adverse events (classified according to grade), sorted by study arm. Brief clinical descriptions of key events will also be provided. If concerns arise from these interim reports, they will be forwarded to the full DSMB for review.

In the event of study termination, formal reports will be submitted to the DAIDS, NIAID, and local IRBs.

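### Table 10's stopping bounds rest on an information schedule that fits no accrual in the protocol and contain misprints; used as printed, they give a two-sided type I error of about 5.6–5.7%, not 5%

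*Protocol*

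**What the plan says.** Section 10.3.1 plans annual interim analyses of the main outcome. Each compares a standardized statistic with a nominal critical value from an error-spending function, citing Table 10. The table's caption reads "This analysis assumes α=0.05 (two-sided test), O’Brien-Fleming boundaries (DeMets error-spending function"), with 350 participants and "a rate of progression of 50% per year in the reference group and 25% per year in the treated group".

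The last two rows of the table, from the Information column onward, read "0.76 | -2.2759 | 2.2550 | 0.01681 | 0.24420" and "0.83 | -1.9851 | 1.9612 | 0.02558 | 0.05000". The columns are information, lower bound, upper bound, alpha and cumulative alpha.

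Section 10.3.2 says that the DSMB's decision to stop "will be guided by the critical values shown in Table 10", and that crossing the boundary stops the study.

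Section 10.1 works from different rates: "In one scenario, the rate of disease progression in the reference group was 50% at two years". The legend to Figure 5 gives scenario A as "50% disease progression by 2 years in reference group" and scenario B as "50% disease progression by 3 years in reference group, i.e., slower disease progression than expected". Both use a 35% effect size, three years of accrual, 5% dropout per year and constant hazards. The synopsis gives a total study duration of five years.

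**The concern.** The table that guides stopping disagrees with the sample-size section about how fast events arrive, and its columns do not agree with each other. In a group-sequential test the late bounds depend on how much information has accrued by each look. If the early share is overstated, successive statistics are taken to be more highly correlated than they are, and the last critical values come out too small. Three features can also be seen on the page: the bounds of a symmetric two-sided test are asymmetric, a cumulative quantity falls from 0.24420 to 0.05000, and the information ends at 0.83. At stake is whether the primary comparison holds its stated 5% level if the printed numbers are used.

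**Working it through.** **1. Rates.** At 50% per year the reference group reaches 1 − 0.5² = 75% by two years and 1 − 0.5³ = 87.5% by three, against 50% in section 10.1. The caption's hazard ratio is ln(0.75)/ln(0.50) = 0.415 (0.50 as a simple ratio). A 35% effect size, read as one minus the hazard ratio, is 0.65. The effect-size formula is missing from the text, so that reading is an assumption.

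**2. Reproducing the table.** The two-sided O'Brien-Fleming-type spending function is α(t) = 4[1 − Φ(z₀.₉₈₇₅/√t)]. At t = 0.2, 0.4, 0.6, 0.8, 1.0 it gives 0.00000, 0.00079, 0.00762, 0.02442, 0.05000. The increments match the printed Alpha column. The year-4 cumulative value is therefore 0.0244 (0.00762 + 0.01681 = 0.02443, the difference being rounding), not 0.24420.

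Spending on the Time column, with correlations from the Information column, recursive integration gives ±4.8769, ±3.3570, ±2.6728, ±2.2759, ±1.9851. These are the printed lower bounds to within 0.0001. The printed upper bounds at looks 3–5 are 2.6724, 2.2550 and 1.9612; the last two are clearly off.

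**3. Information schedule.** Only ratios to the last look matter: 0.29/0.83, 0.50/0.83, 0.62/0.83, 0.76/0.83 and 1, that is 0.35, 0.60, 0.75, 0.92, 1.00. For comparison I used uniform entry over three years, five years in total, 175 per arm and dropout hazard d = −ln(0.95). With H = h + d and a = min(c, 3), the probability of an observed event by year c is

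(a/3)·(h/H)·[1 − (e^(−H(c−a)) − e^(−Hc))/(H·a)].

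| Assumption | Yr 1 | Yr 2 | Yr 3 | Yr 4 | Yr 5 | Events at yr 5 |
|---|---|---|---|---|---|---|
| Table 10, rescaled | 0.35 | 0.60 | 0.75 | 0.92 | 1.00 | – |
| 50% at 2 years, HR 0.65 | 0.07 | 0.27 | 0.55 | 0.81 | 1.00 | 199 |
| 50% at 3 years, HR 0.65 | 0.07 | 0.25 | 0.52 | 0.79 | 1.00 | 153 |
| Caption, 50% vs 25% per year | 0.09 | 0.32 | 0.61 | 0.86 | 1.00 | 249 |

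The column fits neither set of rates. It lies near 1 − 0.5^(t/2) = 0.29, 0.50, 0.65, 0.75, 0.82, which is the reference-group progression in scenario A if everyone had entered at time zero. That origin is a guess.

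**4. Type I error if the printed bounds are applied as they stand.**

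| Information schedule | Printed bounds | Lower column mirrored |
|---|---|---|
| Table's own column | 5.14% | 5.00% |
| Equal spacing (Time column) | 5.60% | 5.45% |
| 50% at 2 years, HR 0.65 | 5.64% | 5.50% |
| 50% at 3 years, HR 0.65 | 5.73% | 5.59% |
| Caption rates, 3-year accrual | 5.45% | 5.31% |

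With event accrual under the null at section 10.1's reference rates, the printed bounds give 5.59% and 5.70%. The two columns differ by about 0.14 points, which is what the misprinted upper bounds contribute. The rest comes from the schedule.

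**5. Corrected bounds.** Keeping calendar-time spending but using section 10.1's event fractions gives ±4.877, 3.357, 2.690, 2.305, 2.031 (50% at 2 years). For 50% at 3 years the final bound is 2.040.

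**The case against.** The strongest reply is that error spending exists so that bounds can be recomputed at the information actually observed. Section 10.3.1 speaks of a critical value calculated with the spending function from accrued data. On that reading Table 10 is only illustrative, the level stays at 5%, and the mechanics may be left to an SAP. This stands as a condition on the result. It does not dispose of the point: section 10.3.1 cites Table 10 for the critical value, section 10.3.2 sends the DSMB to the values shown there, and the protocol nowhere says that they are recalculated.

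Four stronger readings are tempting and are not supported:

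- A reader might infer that the caption's rates produced the inflation. The Information column does not follow from those rates. Replacing them with section 10.1's moves the printed bounds' error only from 5.45% to 5.64–5.73%.
- A reader might infer that an information value of 0.83 at the last look inflates alpha. It does not: dividing the column by 0.83 leaves the bounds and the crossing probability unchanged.
- A reader might take 0.24420 to mean that 24% of alpha is spent by year 4. It is a slipped decimal, evident from its own row, and no stopping rule uses that column.
- A reader might take 1.9612 or 1.9851 as the fixed threshold for the primary analysis. Table 10 is titled as a schedule of interim analyses, and the primary analysis in section 10.2.2.1 does not cite it. Treating look 5 as final is an inference that the protocol should confirm.

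**Conclusion.** Table 10 is wrong as printed and should be corrected. Its caption contradicts section 10.1, its information schedule matches no accrual that the protocol describes, its upper bounds at looks 3–5 do not mirror the lower ones, and one cumulative alpha is misplaced by a factor of ten.

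The effect on the level is moderate and conditional. If the printed bounds are used without recalculation, two-sided error is about 5.6–5.7%, an excess of 0.6–0.7 points. This assumes section 10.1's hazards, uniform three-year entry, a five-year study, 5% yearly dropout and five looks with the fifth as the final one. On the table's own Information column the excess is 0.14 points. The documents do not support a flat statement that the trial fails to hold 5%; they do support the statement that the only critical values the protocol prints would fail to hold it.

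**What to change.** - Recompute Table 10 from section 10.1's hazards and accrual, with symmetric bounds. With calendar-time spending these are about ±4.877, 3.357, 2.690, 2.305, 2.031 for 50% at two years, with a final bound of 2.040 for 50% at three years.
- Define information as observed events divided by events expected at the end, so that it ends at 1.
- Correct year-4 cumulative alpha to 0.0244.
- Reconcile the caption's progression rates with section 10.1.
- State that bounds are recalculated from the spending function at each look from the observed event information, that the printed values are for planning, and that look 5 is the final analysis. Say whether alpha is spent on calendar time or on the event fraction. The final bound is near 2.03–2.04 either way.

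The cost is one table, a few sentences and a slightly stricter final critical value. Take 199 events and a hazard ratio of 0.65. The expected final Z is √(199/4) × 0.431 = 3.04, so a single test at 1.96 has power Φ(1.08) = 86.0%, and crossing 2.031 at the last look alone has probability Φ(1.01) = 84.3%. Earlier looks can also cross, so the loss against a fixed-sample test is at most about 1.7 points.

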10.3.2 Stopping Rules

The DSMB will determine whether to stop the study after a thorough review of interim data. The DSMB’s decision to stop the study will be guided by the critical values shown in Table 10. If, during an interim analysis, the critical value crosses the O’Brien-Fleming boundary, then the study will be stopped on statistical grounds as a significant difference between arms will have been observed. To evaluate trends in adverse events and deaths between the annual reviews of the DSMB, the study team will provide interim safety reports to the DAIDS Medical Monitor, and possibly a DSMB representative, pending discussion of the overall safety monitoring plan with the DSMB committee. These reports will provide cumulative enrollment figures, cumulative deaths and adverse events (classified according to grade), sorted by study arm. Brief clinical descriptions of key events will also be provided. If concerns arise from these interim reports, they will be forwarded to the full DSMB for review.

In the event of study termination, formal reports will be submitted to the DAIDS, NIAID, and local IRBs.

# 11.0 REGULATORY CONSIDERATIONS

## 11.1 Case Report Forms

All data will be recorded legibly in black ink on study forms. Corrections will be made by drawing a single horizontal line through the error (so that the original notation remains clearly legible). The correct information will be written near the original entry and dated and initialed by the investigator or designee.

All study documents, including patient records, laboratory data, and correspondence must be retained by the investigator for at least 5 years or until notification by or transfer to the study sponsor. All study documents are subject to inspection by the study Sponsor and appropriate regulatory authorities.

## 11.2 Monitoring

The study will be monitored by a representative of the Sponsor (Division of AIDS, NIAID, National Institutes of Health - US) to assure accurate and adequate data collection. The investigators will assist in making all study documents requested by the monitor available for review. Arrangements for monitoring visits will be arranged in advance between the investigator and the sponsor, except in the case of an emergency.

## 11.3 Institutional Review Board (IRB)

The protocol and informed consent document and any subsequent amendments will be reviewed and approved by the Institutional Review Boards or Ethics Committees of the Joint Clinical Research Center, Case Western Reserve University – University Hospitals of Cleveland, University of California, San Francisco – San Francisco General Hospital Campus at UCSF. Written documentation of approval of both the protocol and the informed consent must be provided to the TBRU Coordinating Center and Data Center at UCSF before starting the study.

The site Principal Investigator will ensure that an Ethics Committee/IRB will be responsible for the initial and continuing review and approval of the proposed clinical study. The site Principal Investigator or designee will promptly report to the Ethics Committee/IRB all changes in the research activity and all unanticipated problems involving risks to human subjects or others, and will not make changes in the research protocol without Ethics Committee/IRB approval, except where necessary to eliminate apparent immediate hazards to human subjects.

## 11.4 Data and Safety Monitoring Board

An independent Data and Safety Monitoring Board will be appointed by the Sponsor to monitor the study. The DSMB will meet at least annually and will be provided with updated information on the status of the study by the Sponsor (as provided by the PI) prior to each meeting. The principal investigator and other study personnel will be kept blinded to interim study data or analysis that is sorted by study arm. The study’s statistician, however, will have access to this information as needed for the analysis.

## 11.5 Informed Consent

Each study subject will give written informed consent (Appendix VIII and IX) both for the screening process to determine trial eligibility and for participation in the study. The informed consent documents will be translated into the major local language(s) and back‑translated to check for accuracy.

Informed consent will be obtained by a member of the study team, including the investigators or by professional staff supervised by the investigators, after verbal and written explanation of the study as described in the consent form. A copy of the informed consent document will be given to the subject. Appropriate pre‑ and post‑HIV‑test counseling of all study subjects will be performed by trained staff. Interpreters will be used as necessary. Subjects will have an opportunity to ask questions and raise any concerns about the study with the investigator and other study personnel. The informed consent document will be signed and dated (including the time the form is signed) by the subject and the investigator.

The investigator will insure that the purpose of the study is explained to the patient and that written consent is obtained prior to participation in the study. The patient, investigator, and others as required by local regulatory guidelines will sign the consent prior to entry into the study. The patient will receive a copy of the consent form. The investigator will retain a copy of the signed consent forms, which may be inspected at the monitor or auditor’s request.

**11.6 Amendments**

The study sponsor will be notified of any amendments to the study protocol. All protocol amendments will be submitted to the appropriate IRB(s) and Ethics Committees (Section 11.3) for review and will be approved prior to implementation at the study site except if necessary to implement a safety issue. The Principal Investigator at each clinical trial site will provide copies of the Ethics Committee approvals of amendments and any resultant revisions to the informed consent to the TBRU Coordinating Center at Case Western Reserve University.

## 11.7 Protocol Deviations

The study will be conducted as described in this protocol except in emergency situations in which the safety and well-being of a study subject requires immediate intervention in the judgment of the study site physician. Protocol deviations will be reported to the Coordinating Center and NIAID using the specified Protocol Violation/Deviation Form. Deviations should be reported to the Coordinating Center within 2 working days of the site staff learning of the event, and the Coordinating Center will in turn report these to NIAID within 2 working days following receipt.

## 11.8 Confidentiality

The Principal Investigator at each study site will ensure that all study records are managed in a secure and confidential fashion. Study identification numbers and subject initials will be used as identifiers on CRFs, clinical specimens, and computerized databases containing study information. Personal and medical information regarding study subjects will not the released to anyone other than authorized study personnel, the National Institutes of Allergy and Infectious Diseases and its authorized monitoring contractors, the Ethics Committees and Institutional Review Boards of the participating institutions, the OHPR, without the written permission of the subject. Study records will be secured in locked file cabinets at the clinical site.

